**Summary**

**Protocol title:** **An open trial of guided iCBT education to determine the benefits of the Wellbeing Course for consumers of the Mental Health Association with symptoms of anxiety**

**Protocol version:** 1.0

**Objectives:** **Primary objectives:** To determine the short and medium term efficacy of the online eCentreClinic Wellbeing Course to MHA consumers, when administered by the MHA.

**Secondary objective:** To determine the acceptability of the online eCentreClinic Wellbeing Course, to MHA consumers.

**Study design:** Open trial design with one group.

**Planned sample size:** The design (see Stat considerations, below) requires a minimum sample size of 15, but 20 will be recruited.

**Selection criteria:** Australian adults aged 18-64 with a principal complaint of symptoms of anxiety (not OCD).

**Study procedure:** Consumers contacted the Mental Health Association (MHA), NSW, telephone support line will be informed about the study. Interested consumers will be sent an Information and Consent Form. Those who return the completed Consent Form will be contacted by an MHA Psychologist who will telephone the applicant and administer a screening questionnaire. Eligible applicants will be sent login codes to access an online education course, designed to help people learn to manage symptoms of anxiety. This evidence-based course, the Wellbeing Course, includes five online lessons and homework assignments, and all participants will receive weekly contact from the MHA Psychologist to provide support and guidance.

Participants will complete questionnaires at pre-treatment, post-treatment, and then at 2 month follow-ups. Participants will also complete two brief questionnaires before each of the 5 lessons.

**Stat considerations**: With respect to power, a sample size of 15 is sufficient (power at 80%, and alpha at 0.05) to detect pre-post within group differences in effect size of 0.7, which is considered the minimum based on our previous studies.

Analyses will be conducted using parametric techniques and intention-to-treat and completer models.

**Duration of the Study:** 12 months

TABLE OF CONTENTs PAGE

1. BACKGROUND 5

1.1 Disease Background 5

1.2 Rationale for Performing the Study 5

1. BACKGROUND

## Disease Background

Anxiety disorders affect approximately 14% of the adult population annually and are associated with disability, reduced quality of life, and chronicity. Anxiety can be treated effectively with pharmacotherapy and psychological treatments such as cognitive behavioural therapy (CBT). However, less than 50% adults with anxiety seek treatment each year. Barriers to accessing treatment include the direct and indirect costs of treatment, the limited number of trained mental health professionals, and stigma. [1].

## Rationale for Performing the Study

Internet-delivery of CBT (iCBT) is one strategy for improving access to evidence-based treatment for anxiety disorders [2-4]. The CI and his team have now completed 30 trials of iCBT with more than 2200 Australian adults with depression and anxiety disorders. All trials have resulted in clinical outcomes at least comparable to those obtained from good face-to-face treatments, with high levels of acceptability to consumers. The Mental Health Association (MHA), NSW, provides education, advocacy, and support to consumers with anxiety. They would like to assist consumers to access evidence-based resources.

The planned project is a collaboration between the MHA and eCentreClinic at the Centre for Emotional Health (CEH), Macquarie University. This initial study will examine the feasibility of the MHA administering the online interventions developed at the eCentreClinic. This will be achieved through this initial trial, which utilises an open-trial design with a small number of participants (n=20), who will be recruited and managed by an MHA Psychologist, using software and an online course developed by the eCentreclinic.

**Outcome Measures:** Primary and secondary outcome measures will be administered.

The primary outcome measure is:

- Generalized Anxiety Disorder-7 Item Scale (GAD-7) [5]: Measures general symptoms of anxiety. The GAD-7 is sensitive to symptoms of anxiety disorders.

The secondary outcome measures are:

- Patient Health Questionnaire-9 Item (PHQ-9) [6]: Measures symptoms of major depressive disorder.
- Kessler 10-Item (K-10) [7]. Measures symptoms of psychological distress.
- Treatment satisfaction measures [developed by the researchers]: Measures satisfaction with treatment.
- The Things You Do Questionnaire [developed by the researchers]: Measures frequency of adaptive behaviours performed by a participant in the previous week.

In addition, the GAD-7 and PHQ-9 will be administered at the beginning of each lesson to monitor anxiety and mood.

# STUDY OBJECTIVES

## Primary Objectives and hypotheses and endpoints

To determine the short and medium term efficacy of the online eCentreClinic Wellbeing Course to MHA consumers, when administered by the MHA.

These objectives will be achieved by comparing symptom levels (primary and seconday outcomes measures) at each timepoint.

The main hypothesis is that

1. Large effect sizes will be found pre-post, with gains sustained at 2-month follow-up

The Primary Endpoint coincides with the post treatment questionnaires at week 9.

The Secondary Endpoint occurs at 2-month follow-up.

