## Study groups

This design comprises only one group.

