# Participant selection

## Inclusion criteria

(1) Resident of Australia,

(2) 18-64 years of age,

(3) not currently participating in CBT for target symptoms,

(4) a score above 4 on the GAD-7 (indicating at least mild anxiety),

(5) provides informed consent,

(6) access to a computer, printer, and internet

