# Study OUTLINE

## Study Flow Table

| **Dates** | **Phase** | **Activities** |
| --- | --- | --- |
| June-July 2012 | Recruitment | Eligible applicants recruited by MHA |
| August 2012 | Intervention | Participants begin intervention (8 week Course).  Complete outcome questionnaires at pre-intervention  Complete GAD-7 and PHQ-9 before each lesson  Weekly contact from MHA Psychologist |
| October | Post-Intervention | Participants complete intervention.  Complete outcome questionnaires at post-intervention  Telephone feedback from MHA Psychologist |
| December | 2-month follow-up | Complete outcome questionnaires at 2-month follow-up  Telephone feedback from MHA Psychologist |
| February | Write-up | Write up of results and submission of manuscript for publication |
| May | Project Close-Out | Submit final report to MQ HREC  Submit reports to MHA and eCentreClinic |

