## Investigation plan

An open trial, with 1 group (n=20).

This design tests the short and medium term efficacy of the online eCentreClinic Wellbeing Course to MHA consumers, when administered by the MHA.

MHA consumers aged 18-64 years who telephone the [name] Anxiety Support line, will be informed about the aims of the study, and invited to apply. Those interest will be provided with more information and then sent an informed consent form, and asked to complete and return this. Those who complete the form will be telephoned by a Psychologist at the MHA who will provide more details, and administer the Patient Health Questionnaire-9 Item and Generalised Anxiety Disorder-7 item questionnaires. Applicants with scores too high or too low on these questionnaires will be automatically excluded with clear information about where to get treatment, while eligible applicants will be asked to provide demographic details and contact details for their GP.

Eligible applicants will receive an email confirming their participation and start date of the course. On the start date they will receive login codes and instructions to begin the 8-week course. The first part of the first lesson includes standardized questionnaires of anxiety, depression and disability. Course content includes evidence-based principles of managing anxiety and depression. Each of the five lessons contains a printable homework assignment designed to reinforce the material in the lessons. Participants will receive weekly telephone calls or emails from trained and supervised clinical staff at the MHA who will provide support, encouragement and will answer questions about the content of the Course.

Participants will be encourage to log at least weekly to review course materials. They will be asked to complete the GAD-7 and PHQ-9 before each lesson and all questionnaires at week 9 (i.e., at post-education) and again at 2 month follow up. At post-treatment and follow up, participants will receive a telephone call from the MHA Psychologist summarising their individual results. Post 2-months, they will be emailed a summary of the overall results, will be invited to request copies of any published articles when they become available and will be provided information about how to access further treatment should they want it.

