**MHA Open Trial Telephone Interview**

- Hello it’s XXXXX calling from **the MHA …**

1. I’m calling to complete your application for the MHA online anxiety course. To complete your application I need to ask you some questions about your anxiety and your mood. These will probably take 15 minutes to complete, do you have the time right now?
2. First, I want to thank you for applying to our MHA Wellbeing Course. I know it’s quite difficult for most people to apply / takes a lot of courage to apply.
3. I’ll be doing a lot of the talking for this call, but please stop me anytime to ask questions or clarify anything. Is that ok?
4. To start I need to ask you some preliminary questions to check that the course will be suitable for you.

| 1. | Part of the criteria for the course is that you have reliable access to the internet. Do you have reliable access? | Yes | No |
| --- | --- | --- | --- |
| 2. | The internet course is an education course. It is designed to teach people how to manage symptoms of worry, and stress, and panic and anxiety. Does this sound suitable to you? | Yes | No |
| 3. | The internet course is designed for people for whom anxiety is the main concern. Are symptoms of anxiety your primary concern? | Yes | No |
| 4. | The internet course is not designed for people who have symptoms of OCD. Are symptoms of OCD your primary concern? | Yes | No |
| 5. | The internet course is not designed for people with acute psychosis, who are hearing voices, seeing things that other people don't, or believe things that other people don't. Do you have those symptoms? | Yes | No |
| 6. | The Course will begin on XX and will take 8 weeks. Have you got anything planned (e.g. moving house, surgery, holiday) that will interfere with your participation in the Wellbeing Course for more than 2 weeks over that time? | Yes | No |

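### The primary objective claims efficacy, but one unblinded group compared before and after the Course can show only within-group change

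*Protocol*

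**What the plan says.** Under Primary Objectives and hypotheses and endpoints (section 2), the aim is "To determine the short and medium term efficacy of the online eCentreClinic Wellbeing Course to MHA consumers, when administered by the MHA". The method follows: "These objectives will be achieved by comparing symptom levels (primary and seconday outcomes measures) at each timepoint". The main hypothesis is "Large effect sizes will be found pre-post, with gains sustained at 2-month follow-up", with the primary endpoint at week 9. The Summary states the same objective, and the Investigation plan (section 5) says that the design tests efficacy.

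The Study groups section states "This design comprises only one group", and the section on blinding says there is none. Participants are people who telephone an anxiety support line. They must score at least 5 on the GAD-7, which is also the primary outcome measure.

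The Rationale (section 1.2) describes the work differently, as an initial study of whether the MHA can feasibly run the eCentreClinic's interventions. In section 2, however, feasibility appears only under Additional objectives, below efficacy and acceptability.

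The GAD-7 is taken twice before any Course content is seen. At the telephone screen the MHA psychologist will "administer the Patient Health Questionnaire-9 Item and Generalised Anxiety Disorder-7 item questionnaires". The outcome questionnaires are then completed online at Course start. The Study Flow Table puts recruitment in "June-July 2012" and the start of the Course in August. The only stated use of the screening score is to decide eligibility.

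**The concern.** Efficacy is a statement about what the Course adds to what would have happened without it. A one-group pre-post contrast contains no information on the second part. People who ring a support line tend to do so when they feel worse than usual, so some improvement over the following nine weeks is plausible with no Course at all. The protocol does not mention natural recovery or any limit on reading the change causally.

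What is at stake is the conclusion the trial may publish. With the objective as worded, a clear fall in GAD-7 would answer the efficacy question on paper, although the design cannot answer it. This is protocol content and not a detail to settle in an analysis plan, because no analysis of these data would supply the missing comparison.

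**Working it through.** **1. The plan's own figure.** Sample Size Calculation: 15 participants, 80% power, alpha 0.05, pre-post effect 0.7. Neither the sidedness nor the standardiser is stated. Take 0.7 as mean change divided by SD of change, and use the noncentral t distribution with n − 1 degrees of freedom and noncentrality 0.7·√n.
- One-sided: n = 15 gives 82.4% power and is the smallest n above 80%, so the stated figure is reproduced.
- Two-sided: n = 15 gives 71.3%, and 19 are needed.
- If 0.7 is instead in raw SD units with an assumed pre-post correlation of 0.6, n = 15 gives 80.5% two-sided.

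On any of these readings, the calculation is about showing that mean change differs from zero. It contains no term for change without the Course.

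**2. How often an inert course would look effective.** Let the true Course effect be zero and the untreated improvement be d SD of change. The chance of a significant two-sided paired test is P(|T| > c), where T is noncentral t with n − 1 degrees of freedom and noncentrality d·√n. The critical value c is 2.093 at n = 20 and 2.145 at n = 15. The values of d are assumed.

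| d (assumed) | n = 20 | n = 15 |
|---|---|---|
| 0 | 5.0% | 5.0% |
| 0.2 | 13.6% | 11.2% |
| 0.3 | 24.7% | 19.2% |
| 0.4 | 39.7% | 30.3% |
| 0.5 | 56.5% | 43.8% |

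(The n = 20, d = 0.5 entry is 0.5645 before rounding, hence 56% in whole per cent.)

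**3. Does selection on GAD-7 drive this?** Mostly not. With assumed caller mean 8 to 12, SD 4.5 to 5.5 and retest correlation 0.5 to 0.8, regression to the mean from the entry cut is about 0.1 to 1.2 points (0.02 to 0.23 SD). The cut is applied to the telephone score, while the pre score is a separate later measurement. Most of that fall therefore happens before the pre-post contrast begins. The threat that remains is natural recovery after help-seeking.

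**4. What the screening score could add.** The 95% confidence half-width for the screening-to-start change alone, in SD of change, is t(0.975, n − 1)/√n:
- n = 20: 2.093/4.472 = 0.47
- n = 15: 2.145/3.873 = 0.55

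To use it as a comparison, one would take (start − post) − (screening − start) = 2·start − screening − post. With equal variances σ² and equal correlations r (assumed), its variance is 6σ²(1 − r), against 2σ²(1 − r) for a single change. Its SD is therefore √3 times larger, and the half-widths become:
- n = 20: 0.468 × 1.732 = 0.81
- n = 15: 0.554 × 1.732 = 0.96

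Both exceed the 0.7 design effect. A net effect of 0.7 SD of change becomes 0.7/1.732 = 0.404, which has 40% power at n = 20 and needs 51 participants for 80%. If 0.7 is in raw SD units and r runs from 0.5 to 0.8, power at n = 20 is 40% to 77%.

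**The case against.** The strongest reply is that *efficacy* is merely loose wording. The document calls itself an open trial, declares one group and no blinding, states its hypothesis as a within-group effect size, and describes an initial feasibility study of 20 people. Nowhere does it say that p < 0.05 will be taken as proof of efficacy. This partly stands: the significance rule in step 2 is an illustration, not a rule in the protocol. If success meant an observed effect of at least 0.8 SD of change (an assumed meaning of *large*, which the protocol does not define), an inert course would reach it at n = 20 in only about 1% to 13% of trials over the same assumed range. But a stricter threshold still does not attribute the change to the Course, and three sections state the aim as efficacy.

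A reader might infer more than the documents support:
- **That an untreated control period of about two months is already available.** Two months is a calendar maximum. Screening follows return of a consent form, recruitment may end once 20 people have joined, and the appendix on the recruitment process aims for a July start. The wait could be short and will vary by person. Nor is it strictly untreated, since the only treatment barred at entry is current CBT.
- **That the pre-treatment score is undefined.** The Study Flow Table, the Investigation plan and the confirmation email all place the questionnaires at Course start.
- **That current CBT goes unchecked.** The inclusion criterion reads "not currently participating in CBT for target symptoms". The six scripted items introduced by "To start I need to ask you some preliminary questions to check that the course will be suitable for you" do not ask about it. However, the Recruitment Process and Telephone Interview section lists it among the criteria the call must check. Age and residency are likewise listed there and not scripted.

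**Conclusion.** The point holds as a matter of what the trial may conclude. As worded, the primary objective promises an answer about efficacy that one unblinded group followed over time cannot give, and it sits awkwardly with the feasibility purpose in the Rationale. This rests on the design alone and needs no assumption.

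The size does rest on an assumption. For untreated improvement of 0.2 to 0.5 SD of change, a significant pre-post fall would occur in 14% to 56% of trials of an inert course at n = 20 (11% to 44% at n = 15). The documents give no figure that would narrow this range. It would be wrong to go further and say that the entry cut on GAD-7 materially inflates the pre-post contrast, or that the screening score could turn this into a controlled comparison. Step 3 speaks against the first and step 4 against the second.

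**What to change.** Reword the objective in the Summary, in Primary Objectives and hypotheses and endpoints, and in the Investigation plan. A suitable form is: to estimate within-group change in symptoms during and after the Wellbeing Course when it is run by the MHA. Add one sentence saying that, without a comparison group, the change will not be attributed to the Course. The hypothesis about pre-post effect sizes can stay as a within-group statement. The cost is wording only, with no change to sample size, visits or data.

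Optionally, report the change from the telephone-screening GAD-7 to the Course-start GAD-7, with days elapsed and a 95% confidence interval (half-width about 0.47 SD of change at n = 20). The data are already collected. Label it descriptive and state its limits: the wait is variable and possibly short, one score is taken by telephone and the other online, and regression to the mean from the entry cut falls mainly in this interval, so it may overstate untreated change. Do not test the difference between the two changes or present it as a control; at about ±0.81 SD of change it is too imprecise for that.

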## Secondary objectives

To determine the acceptability of the online eCentreClinic Wellbeing Course, to MHA consumers. This objective will be achieved by measuring consumer satisfaction at 9-weeks (1-week post-treatment).

## Additional objectives

To determine the feasibility of the MHA administering online Courses developed by the eCentreClinic.

# STUDY Design

## Design

Open trial design, n=20.

## Study groups

This design comprises only one group.

## Number of participants

20 in total (1 group).

## Number of centres

2, the eCentreClinic, Centre for Emotional Health, Department of Psychology, Macquarie University, and Mental Health Association (MHA), NSW.

## Duration

1 June 2012 - 30 May 2013 inclusive of intervention, 2 month follow up and write up of results. The Primary Endpoint will be the end of active intervention (i.e., 9 weeks after beginning the Course); the Secondary Endpoint will be at the 2 month follow up (i.e., 2 months after completion of the intervention).

# Participant selection

## Inclusion criteria

(1) Resident of Australia,

(2) 18-64 years of age,

(3) not currently participating in CBT for target symptoms,

(4) a score above 4 on the GAD-7 (indicating at least mild anxiety),

(5) provides informed consent,

(6) access to a computer, printer, and internet

## Exclusion criteria

(1) Severe depression (i.e. score > 22 on PHQ-9), suicidal ideation or plan (based on interview),

(2) suicidal intention or plan,

(3) principal problem not anxiety,

(4) principal problem are symptoms of OCD,

(5) acute psychosis.

# Study OUTLINE

## Study Flow Table

| **Dates** | **Phase** | **Activities** |
| --- | --- | --- |
| June-July 2012 | Recruitment | Eligible applicants recruited by MHA |
| August 2012 | Intervention | Participants begin intervention (8 week Course).  Complete outcome questionnaires at pre-intervention  Complete GAD-7 and PHQ-9 before each lesson  Weekly contact from MHA Psychologist |
| October | Post-Intervention | Participants complete intervention.  Complete outcome questionnaires at post-intervention  Telephone feedback from MHA Psychologist |
| December | 2-month follow-up | Complete outcome questionnaires at 2-month follow-up  Telephone feedback from MHA Psychologist |
| February | Write-up | Write up of results and submission of manuscript for publication |
| May | Project Close-Out | Submit final report to MQ HREC  Submit reports to MHA and eCentreClinic |

## Investigation plan

An open trial, with 1 group (n=20).

This design tests the short and medium term efficacy of the online eCentreClinic Wellbeing Course to MHA consumers, when administered by the MHA.

MHA consumers aged 18-64 years who telephone the [name] Anxiety Support line, will be informed about the aims of the study, and invited to apply. Those interest will be provided with more information and then sent an informed consent form, and asked to complete and return this. Those who complete the form will be telephoned by a Psychologist at the MHA who will provide more details, and administer the Patient Health Questionnaire-9 Item and Generalised Anxiety Disorder-7 item questionnaires. Applicants with scores too high or too low on these questionnaires will be automatically excluded with clear information about where to get treatment, while eligible applicants will be asked to provide demographic details and contact details for their GP.

Eligible applicants will receive an email confirming their participation and start date of the course. On the start date they will receive login codes and instructions to begin the 8-week course. The first part of the first lesson includes standardized questionnaires of anxiety, depression and disability. Course content includes evidence-based principles of managing anxiety and depression. Each of the five lessons contains a printable homework assignment designed to reinforce the material in the lessons. Participants will receive weekly telephone calls or emails from trained and supervised clinical staff at the MHA who will provide support, encouragement and will answer questions about the content of the Course.

Participants will be encourage to log at least weekly to review course materials. They will be asked to complete the GAD-7 and PHQ-9 before each lesson and all questionnaires at week 9 (i.e., at post-education) and again at 2 month follow up. At post-treatment and follow up, participants will receive a telephone call from the MHA Psychologist summarising their individual results. Post 2-months, they will be emailed a summary of the overall results, will be invited to request copies of any published articles when they become available and will be provided information about how to access further treatment should they want it.

The intervention Course will be delivered via the website [www.ecentreclinic.org](http://www.ecentreclinic.org). This Course consists of 5 online lessons, homework assignments, and weekly support, conducted over an 8 week period:

1. *Lesson One:*
   1. Learn about the physical, cognitive and behavioural symptoms of anxiety and depression Learn about the principles of CBT
2. *Lesson 2:*
   1. Learn about the relationship between the way you think and feel
   2. Begin monitoring and challenging unhelpful thinking patterns.
   3. Examples based on people with symptoms of anxiety and depression.
3. *Lesson 3:*
   1. Learn about physical symptoms and managing these with de-arousal and activation techniques
   2. Assertiveness skills
   3. Examples based on people with symptoms of anxiety and depression.
4. *Lesson 4:*
   1. Learn about behaviours (low activity and avoidance) that make symptoms worse, and how to challenge those behaviours
   2. Examples based on people with symptoms of anxiety and depression.
5. *Lesson 5:*
6. Learn about problem solving, relapse prevention and staying well
7. Examples based on people with symptoms of anxiety and depression.

At the beginning of the Course all participants will complete the outcome measure questionnaires. The questionnaires being administered in this study are all valid and reliable clinical and research measures.

All participants will complete a second entire set of questionnaires at the post-treatment point (Primary Endpoint), and at the 2 month follow-up (Secondary Endpoint).

In addition, brief measures of anxiety and depression (the GAD-7 and PHQ-9) will be administered at the beginning of each lesson to monitor anxiety and mood. We will also encourage feedback from participants at every stage of the project to determine how to improve the content and delivery of Course.

